## Abstract

**Background:**

Venous leg ulcers are slow-healing wounds with a high recurrence rate of 70% and a 60% risk of becoming chronic. Signs and symptoms such as pain or exudate are not only a burden on those affected but also on the healthcare system and society in general. The estimated leg ulcer prevalence in the general population is 1%. Treatment costs for leg ulcers are estimated to be 3% of overall health expenditure. Current therapeutic approaches are multifaceted and include compression therapy, leg elevation, specific ankle-exercises and a protein diet. They require an interdisciplinary team of health care professionals. Approximately 70% of patients have a knowledge deficit with regards to therapeutic measures and have difficulties with adherence to treatment protocols. Therefore, it is of utmost importance that the treatment team provides effective patient education and support during the learning phase. However, there is little evidence and no published studies that describe and evaluate effective interdisciplinary educational interventions that target compliance/adherence to the treatment plan in patients with leg ulcers. We therefore propose to develop an evidence-based interprofessional educational intervention and evaluate its feasibility first in a pilot study and subsequently in a randomized controlled trial.

**Method/Design:**

First, the development of an evidence-based educational intervention in collaboration with an expert panel is proposed and second, a randomized controlled feasibility study in a wound-care outpatient clinic. Eligible patients (*n* = 20) with leg ulcers will be randomized to receive either interdisciplinary education and usual care or only usual care, for 12 weeks. Data will be analyzed using SPSS version 25. Univariate and bivariate analysis will be conducted according to the data level and distribution of the data.

**Discussion:**

We will first develop an evidenced-based educational intervention and second, we will examine the feasibility of implementing this educational intervention in a realistic care context in patients with leg ulcers. The results will inform the final design of a subsequent randomized controlled trial, which will examine the effectiveness of the educational intervention. An intervention that enhances patient adherence to therapy would be beneficial to individual patients and to society as a whole.

**Trial registration:**

ClinicalTrials.gov, NCT03454698. Registered on 6 March 2018.

**Electronic supplementary material:**

The online version of this article (10.1186/s13063-019-3333-4) contains supplementary material, which is available to authorized users.

## Background

Venous leg ulcers (VLU) are poorly healing wounds caused by chronic venous insufficiency (CVI) [1]. CVI is a form of peripheral vascular disease that originates from an obstruction of the venous system or a defective venous valve, leading to edema, venous hypertension, skin inflammation and finally to venous leg ulcers [2]. Of all poorly healing wounds 60% are attributable to VLU [3]. Healing times are long with 60% of these wounds healing within 6 months and another 33% within 1 year. The wound never closes in 7% of cases [4]. Up to 70% of patients with leg ulcers suffer a recurrence within 3 months after wound closure [5–7]. Hence, VLU is a health problem that affects most patients for life [8].

Epidemiological data from industrialized countries including the USA and Scandinavia have shown that the prevalence of leg ulcers is 1% in the general population and 3% in people over 80 years of age [9]. An extrapolation of these findings to the Swiss context would suggests that there are an estimated 84,000 to 94,000 people suffering from VLUs, of whom 12,500 are above 80 years of age [10].

Consequently, these chronic wounds are a burden not only on the affected persons themselves, requiring expensive treatment, but also on society as a whole, as an estimated 2–3% of all health expenditure covers the treatment of this condition [9]. With a Swiss health budget of nearly 78 billion Swiss francs in 2017, this would translate into an annual cost up to 3 billion Swiss francs [11].

## Current treatment of venous leg ulcers

Standard care for the treatment and prevention of VLU includes compression therapy, elevation of the leg, exercises in the foot region, ambulating and a balanced diet rich in proteins and vitamins [12–16]. The therapeutic approach to the management of VLU is a multifaceted approach targeting the management of risk factors associated with prolonged healing times and recurrence. As patient adherence to the care plan is an essential factor in leg ulcer healing and in the prevention of recurrent ulcers, the individual components and factors associated with non-adherence are of interest. Most of the evidence on adherence originates from small studies and there are no published results from large-scale studies. The following sections reflect published evidence on measures taken to prevent recurences.

### Adherence to and patient knowledge of compression therapy

#### Adherence to compression therapy

A systematic review found that patients’ adherence to compression therapy varies widely between 10% and 80% [17]. Findings showed that non-adherence to compression therapy is associated with delayed wound healing and equates to a 2–20-fold increase in recurrence [18]. The literature cites a lack of patient knowledge of adherence to treatment as a reason for non-adherence [19–21]. For example, Edwards and colleagues [19] showed that because of these knowledge deficits, only 27% of patients with leg ulcers wear compression stockings. One reason given for patients’ knowledge deficit is lack of education by professionals during delivery the of care, due to a lack of up-to-date information and appropriate time resources to provide the required education [22].

#### Interventions to improve adherence and knowledge

Intervention studies seeking to influence adherence to compression therapy and other aspects of the treatment were carried out by Heinen and Brooks. Based on their identification of factors for non-adherence, Heinen and co-workers developed and evaluated a counselling program aimed at improving the adherence to compression therapy and physical activity in patients with leg ulcers (“Lively Legs”) [23]. Treatment adherence was surveyed using patient interviews. One of the main findings was that although an increase in adherence was observed after 18 months in both groups (from 37% to 46% in the intervention group and from 27% to 45% in the control group), no significant or relevant difference was found between the groups. These findings might first be explained by the fact that the patients’ wound status was different at baseline—overall 68% had an open wound, while in 32% of patients the wound had already closed—and second by the fact that the overall dropout rate was 26%.

An educational intervention was examined in a study by Brooks and co-workers [24]. The subjects in the control group wore the compression stockings for an average of 3.3 h per 24 h longer when compared to the intervention group. No published studies describe any successful and/or feasible interventions that increase adherence to compression treatment.

### Adherence to and knowledge of elevation of the legs and physical activity (walking and foot exercises)

#### Adherence to leg elevation and physical activity

In addition to adherence to compression therapy, the recurrence rate of leg ulcers is associated with elevating the legs to heart level for 30 min three to four times a day [25] and with regular isometric exercises. Brooks and co-workers [24] found that patients who had been educated to elevate their legs did this for 2 h longer per day than the control group, which had received no such guidance (*f* = 2.88, *p* = 0.015). A further measure described in the literature as reducing recurrence is to instruct patients to ambulate for 150 min a week (30 min, 5 days per week) at slow to medium pace to increase blood flow [26].

Isometric exercises in the ankle area are another way to prevent recurrence of leg ulcers. Van Hecke and co-workers [27] observed an increase in adherence to foot exercise regimes from 0 at baseline to 17 after 3 months (*p* = 0.003; Z = − 2.97). Kelechi and co-workers [28] observed an improvement in eversion of the right ankle by a mean of 1.3 (SD = 13.0; *p* = 0.543) following three home visits and three Skype consultations, in a small study of 21 participants.

### Adherence to and knowledge of nutritional recommendations

#### Adherence to nutritional recommendations and relationship to wound healing

The patient’s diet and nutritional status are strongly associated with wound healing. Older adults’ adherence to nutritional recommendations is often insufficient due to their comorbidities, multiple medication usage, chewing and swallowing difficulties, physical limitations, limited access to healthy foods or a lack of social support [29, 30]. Malnutrition amongst older adults in general has been described but is still unaddressed [31].

Patients with chronic wounds require higher than recommended dietary allowances of nutrients to promote wound healing due to the increased metabolism activated by chronic inflammation and increased cellular activity in the wound. Possibly there is a discrepancy between nutritional needs and food consumption, especially when it comes to protein intake [31]. Protein deficiencies slow the healing process and the formation of scars, as the formation of connective tissue and collagen synthesis requires the presence of amino acids such as arginine or cysteine [32, 33]. Patients with protein deficiency are advised to increase their daily protein intake to 1.2–1.5 g/kg body weight.

#### Education for leg ulcer patients

The literature indicates that patients with VLUs do not have sufficient knowledge of the pathophysiology of their condition or of preventive measures to perform effective self-management [1, 2, 20, 34]. Since knowledge of preventive and therapeutic measures is a prerequisite for their implementation, education and support from healthcare specialists is essential.

Successful educational interventions are described in populations with other conditions like diabetes mellitus or asthma [35, 36]. However, there are few data on the effectiveness of educational measures in patients with venous leg ulcers. In particular there are no data on educational measures targeting improvement of patients’ knowledge of the etiology/pathophysiology of their disease and their adherence to customized treatment measures. Because patients are often left on their own after their ulcer has healed and have to take sole responsibility for their leg care, this education should take place before the completion of treatment. Due to their close therapeutic relationship, wound-care specialists are predestined to offer this educational training. The education aims to improve the adherence to treatment recommendations.

The few studies available show that the recurrence rate can be reduced by up to nine times by providing education [24, 37]. O’Brien and co-workers [38] performed a qualitative study, interviewing 10 patients about their attitudes to physical exercise. The results showed that patients learnt to understand the relationship between the wound and their adherence to treatment. A randomized controlled trial showed that by educating the patient, the recurrence rate was reduced from 36% to 4% within 1 year (log rank test = 8.28, *p* = 0.004) [24]. A recent randomized controlled feasibility trial using a 12-week supervised exercise program as adjunct therapy to compression in patients with VLU showed that due to exercises the healing rate was higher in the intervention group (83% vs. 60%) [39]. There is no published evidence on the effectiveness of interprofessional interventions in patients with VLU.

### Study objectives

The aim of the protocol is (1) to develop an interdisciplinary educational intervention (nursing, physical therapy and nutrition) and (2) to evaluate the feasibility of implementing it for patients with VLUs and compare their adherence to therapy to that among patients receiving standard care. The results from this pilot study will inform the design of the main study, which will measure the effectiveness of this interdisciplinary intervention.

## Methods: participants and interventions

The TIEIVLU study is a project with two parts. First is the development of an evidence-based interprofessional patient education intervention and second is the implementation of the intervention and testing of its feasibility and acceptability.

A small-scale single-center, randomized, controlled trial is proposed as a pilot to the main study. Randomization will occur at the subject level, Feasibility and acceptability will be measured using the participation rate and the completeness of the data.

The educational intervention will be developed at the School of Health Sciences, HES-SO University of Applied Sciences and Arts, Geneva. The content of this educational tool is to improve patient’s knowledge and self-efficacy and subsequently adherence to comprehensive treatments such as compression therapy, leg elevation, physical activity and nutrition.

### Setting

The pilot study will be conducted in one outpatient wound-care clinic in western Switzerland. This outpatient wound-care center specializes in the care of patients with leg ulcers. Their staff are interested and experienced in the conduct of scientific studies. The participating outpatient wound-care center treats 45–66 patients with leg ulcers every year.

### Eligibility criteria

The following inclusion criteria apply to participants in this study:An existing open venous leg ulcerAn ankle brachial pressure index (ABPI) between 0.8 and 1.3Age over 18 yearsProficiency in the French language

In addition, the following exclusion criterion applies:Valid informed consent is not or cannot be given

### Groups

A randomized controlled pilot trial with three measurement points will be carried out over 3 months to evaluate whether the intervention sustains an effect on the participants’ adherence to treatment. (Fig. 1). The control group (CG) will receive usual care. “Usual care” for patients in the CG is defined as follows: visits to the outpatient wound-care center as directed by a physician and wound care performed by the wound expert according to the hospital’s own standards. This standard corresponds to the one from the European Wound Management Association (EWMA).

**Fig. 1 Fig1:**
[figure not shown]
Randomization and data collection

The intervention group (IG) will receive usual care plus the educational intervention: “usual care” as described for the CG also applies to the IG. The intervention will consist of giving patients an opportunity to learn about the use of compression bandages, wearing and putting on compression stockings, physical activity, good skin care and a high-protein, vitamin-rich diet. This group will be supervised by another study nurse (not the nurse who is in charge of the control group).

### Intervention: interprofessional one-on-one educational intervention

The nurse performing the intervention will be a wound expert well-versed in the use of compression bandages, wearing and putting on compression stockings, physical activity, good skin care and a high-protein diet. The intervention nurse will conduct the educational sessions. The content of the educational sessions will be standardized and identical and will cover:Pathophysiology of leg ulcersWearing of compression stockingsIsometrics exercises in the region of the lower extremitiesPhysical activityHigh-protein diet

The educational sessions will follow a standardized protocol.

Patients in the CG will receive usual care at the outpatient clinics. Usual care includes the T = tissue removal, I = infection control, M = moisture balance and E = edge advancement (TIME) strategy proposed by the EWMA [40]. This treatment strategy optimizes the wound-healing process by reducing edema, exudate, and bacteria in the wound.

Patients in the intervention (IG) group will be receiving the same usual care as the patients in the CG. In addition, they will receive training in the following activities at 3-month intervals over 1 year.

#### Putting on and wearing compression stockings

The pathophysiological reasons why clients should be wearing compression stockings will be explained. In addition, each patient will receive an individual demonstration of how to best put on and take off the compression stockings.

#### Exercises in the region of the lower extremities

Patients will be instructed to do regular foot and ankle exercises that can help strengthen the leg muscles and improve blood flow in the legs. While they are sitting (or standing), they have to flex their ankles by pointing their toes away from them and then pointing them up. Patients are instructed to do 10 repetitions of the exercise several times each day [41–43]. These exercises are consistent with the exercises in the guidelines for exercise and physical activity for older adults [44].

#### Physical activity

Patients will receive a wearable Fitbit. A Fitbit is an activity tracker, wireless-enabled wearable device that measures the number of steps walked. Through this technology the numbers of patients’ steps will be calculated and the patient will be reminded to move [45].

#### Elevation

Patients will be advised to elevate their feet to heart level at least 2 h per day.

#### Nutrition

Patients will be educated to eat a protein-rich diet. As with the movement, patients will also be instructed to evaluate their protein intake with the help of a nutrition log. To this end, patients will be educated on the protein content of various common foods.

### Sample

The study participants recruited will be consecutive patients of the participating institution that meet the inclusion and exclusion criteria. For this pilot study 20 patients will be recruited.

### Recruitment

Study participants will be recruited by nursing staff in the participating outpatient wound-care center. Patient lists will be screened daily for potential study participants diagnosed with venous leg ulcers. The nurses will assess the inclusion and exclusion factors for these potential participants and, if inclusion is possible, invite them to participate. Participants will be given 24 h to decide whether or not to participate. After obtaining informed consent, the participants will be referred to the study nurse, who will collect the data at baseline and at further data acquisition times along the timeline (T_0_ to T_3_). In the event that a person declines to participate, a mini-dataset will be collected comprising data on age, gender and reason for refusal. The mini-dataset will not contain health-related data. However, patients will be orally informed that stating the reason for declining to participate is entirely voluntary and that they can have the reason struck from the record at any time.

## Methods: assignment of intervention

### Randomization

After collection of baseline data, participants will be randomly assigned following simple randomization procedures (computerized random numbers) to one of two treatment groups. Gray sealed opaque numbered envelopes will be used. The intervention nurse will open the envelope and allocate the participant to the respective group.

### Blinding

Due to the intervention being an educational program, neither the participants nor the staff performing the intervention can be blinded to treatment allocation. However, the person entering and analyzing the data will be blinded to the participants’ group assignments.

## Methods: data collection, management and analysis

### Data collection

The feasibility (including acceptability) will be measured using the participation rate and the completeness and the acceptability of the intervention. The participation rate is the number of persons participating in the study divided by the number of persons eligible for participation. The completeness is measured by calculating the amount of missing data. The acceptability of the intervention is assessed from the data on self-care in patients with venous leg ulcers, physical activity and quality of life, food intake and nutritional status. The data from the intervention and control groups will be collected by each group’s own trained study nurse. Baseline data will be collected at the outpatient clinic whereas at T_1_, T_2_ and T_3_ the data will be collected during home visits.

At baseline (T_0_), basic demographic data such as age, sex, height, weight, marital status, socioeconomic factors and medical history will be recorded. Diagnostic information on the first occurrence of leg ulcers, venous interventions, deep-vein thrombosis, cardiac situation (chronic venous insufficiency (CVI) severity, Ankle Brachial Pressure Index (ABPI; ABPI = P_leg_/P_arm_), blood pressure, heart rate, edema) and other comorbidities will be obtained from the patient documentation on a single occasion. The data on self-care in patients with venous leg ulcers, physical activity and quality of life, food intake and nutritional status are obtained using instruments specifically validated for these concepts.

Health-related behavior is acquired monthly as a self-report (questionnaire) by the participants. The questionnaire enquires into the following parameters during the previous 24 h:Duration of wearing the compression stockings (in hours)Frequency and duration (time) of the elevation of the leg above heart level (minutes per day)Amount of physical activity (through a Fitbit)Number of foot exercises performed (how many days a week the foot exercises are performed)Nutrition (food intake assessment and nutritional status)Self-care

In addition, the following wound-related data are collected in patients with wounds:Date of recurrenceWound characteristics (size, time to possible healing, wound classification according to Widmer [46])Wound dressings used (including for compression)

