## Discussion

This protocol is designed to develop an interprofessional educational intervention and to examine it in everyday care. If the results of this feasibility study are positive a larger study will be conducted. This larger study will generate new information on the knowledge, attitudes and behaviors of patients with VLU in regards to adherence to treatment recommendations and to what effect these can be modified by an interdisciplinary educational intervention. The results will subsequently inform the development/review of current clinical guidelines. Enhancing patient adherence to therapy is a challenge that is not unique to the care of patients with VLU or the field of wound care. The findings can be applied to patients with other chronic conditions that require close adherence to treatment regimes Additional file 1.

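### Acceptability of the education is defined in two different ways, and neither definition measures it directly

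*Protocol article*

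**What the plan says.** The section Methods: participants and interventions (protocol article) gives the second part of the project as implementing the intervention and testing whether it is feasible and acceptable. It then states: "Feasibility and acceptability will be measured using the participation rate and the completeness of the data".

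The Data collection section gives a different account: "The feasibility (including acceptability) will be measured using the participation rate and the completeness and the acceptability of the intervention". Acceptability is now a third item beside the other two, and the sentence is circular, because acceptability is both included in feasibility and used to measure it. The section then names the source: "The acceptability of the intervention is assessed from the data on self-care in patients with venous leg ulcers, physical activity and quality of life", and continues with food intake and nutritional status. These data, it says, "are obtained using instruments specifically validated for these concepts".

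The other two components are defined. For participation: "The participation rate is the number of persons participating in the study divided by the number of persons eligible for participation". Completeness is the quantity of missing data.

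The Discussion section gives the use of the result: "If the results of this feasibility study are positive a larger study will be conducted".

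**The concern.** A feasibility study of an educational programme should be able to say whether the patients who were offered it attended, kept with it and found it tolerable. Here the two definitions differ, so two people following the article could report different acceptability results from the same data. Neither set of data comes from asking or observing how patients received the education. At stake is the acceptability part of the feasibility result. If it cannot be interpreted, the team plans the larger study without knowing whether patients accept the intervention.

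**Working it through.** No calculation applies: the article gives no acceptability figure, threshold or rate to reproduce. The check sets the passages side by side and asks of each proposed measure whether it can vary with acceptability of the education.

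1. **The two definitions.** Methods: participants and interventions uses participation rate and data completeness for feasibility and acceptability together. Data collection keeps those two and adds acceptability as a separate third component, read from scores. Under the first definition the scores play no part. Under the second, participation and completeness are not the acceptability measure. Both cannot be the definition.

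2. **Participation rate.** Its numerator is people who join and its denominator is people who are eligible. Under Recruitment and Randomization the order is consent, then baseline data, then allocation. The rate is therefore fixed before anyone has received a session. It shows willingness to enter the trial, and at most what people expect of the education.

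3. **Completeness.** This is the amount of missing data, and it covers both groups: "The data from the intervention and control groups will be collected by each" group's own study nurse. It reflects mainly the burden of questionnaires and home visits, which controls carry as well. It registers people who leave the study. It does not register someone who stops the education but stays in follow-up.

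4. **Scores.** Three features count against them.
   - By the article's own statement, the instruments are validated for the concepts they score, and acceptability is not among those concepts.
   - They overlap with what the education is meant to change, which the article describes as knowledge and self-efficacy and "subsequently adherence to comprehensive treatments such as compression therapy, leg elevation, physical activity and nutrition". Physical activity and nutrition appear in both lists, and self-care lies close to them. These are effect outcomes.
   - They are collected in controls too, whose values cannot carry information about an intervention they did not receive.

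   A patient may welcome the education and not improve, or improve and find it burdensome.

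5. **Charitable readings.** If missing answers on these instruments were meant, the same section already counts them as completeness. If behaviour were meant as a proxy for uptake, the article does not say so, nor how a score becomes an acceptability result.

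6. **Reach.** Data collection lists three components: participation, completeness and acceptability. Only the third is affected. It informs the decision in the Discussion section alongside the other two.

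**The case against.** The strongest reply is that the article is a condensed account, and that attendance logs, withdrawal forms, rating scales and numerical thresholds usually stand in a full protocol. That is right, and their absence alone would not be a finding. But the fault lies in what the article states: two definitions that differ, and a data source that does not fit the concept.

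A second reply is that the listed data are not worthless. Study dropout shows partly as missing data at the T1 to T3 home visits. Reasons for refusal are sought from people who decline. Self-care and activity give some indirect sign that patients do what was taught. All of this stands, which is why the claim is only that nothing measures acceptability *directly*.

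A reader might go further and infer that the decision on the main study as a whole rests on an invalid measure. The article does not support this. It has no formal progression rule, only one sentence in the Discussion section. Study objectives says that the results will inform the design of the main study. Two of the three components are properly defined.

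A reader might also infer that acceptability becomes an underpowered efficacy test. With 10 patients per group, the 95% interval for a mean difference has a half-width of 2.10 × √(2/10) = 0.94 SD. The arithmetic is correct, but it assumes a rule that is not in the text. Nothing ties acceptability to a between-group comparison, and the only between-group test described is at T0. Simple randomization does not guarantee 10 per group either.

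Finally, the background section cites 26% dropout in a counselling trial, and a reader might project 0.26 × 20 = 5.2 dropouts here. That trial reported results at 18 months and this one follows patients for 12 weeks, so the projection is not supported.

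**Conclusion.** The point holds in limited form. The article defines acceptability in two incompatible ways, and under either one the acceptability component of the feasibility result rests on an unsuitable measure. This should be corrected before enrolment, because acceptability is part of the pilot's stated purpose. The extent is one of three components, and no numerical size can be attached to it. The wording conflict and the indirect nature of the measures can be read straight from the text. The conclusion assumes that acceptability has its ordinary meaning, namely how patients who are offered the education receive it. It does not extend to participation and completeness as feasibility measures, which are sound.

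**What to change.** - Use one definition of acceptability in both Methods: participants and interventions and Data collection.
- Assess it in the intervention group by attendance at planned sessions, withdrawals with reasons, and a short acceptability rating at the planned T3 visit.
- Report retention in both groups beside participation rate and completeness as feasibility measures.
- Keep self-care, activity, quality of life and nutrition as exploratory outcomes, not as evidence of acceptability.
- If the sponsor wants progression thresholds, it should set them before enrolment. The article offers no basis for particular values.

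Attendance needs a denominator. The section on the one-on-one intervention schedules training every 3 months for a year, whereas the Abstract gives 12 weeks and the Groups section 3 months. These passages must be reconciled so that the number of planned sessions within follow-up is known.

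The cost is protocol wording, simple attendance and withdrawal records, and one short questionnaire at a visit that already takes place. The downside is slightly more patient time at T3.
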